### Objectives {7}

The objective of the present intervention study is to conduct an effectiveness-implementation hybrid trial with co-primary aims of (1) determining BEAM’s effectiveness in improving parent mental health challenges (2) evaluating the implementation of BEAM in community agencies through metrics of feasibility, acceptability, and uptake. With respect to co-primary aim (1), we hypothesize that enrolled parents will evidence improvements in self-reported mental health (primary outcome) across four timepoints. Additionally, we hypothesize that enrolled parents will display reductions in parenting stress and harsh parenting behaviours, and report improvements in child mental health and developmental outcomes (secondary outcomes) across four timepoints. With respect to co-primary aim (2), we hypothesize that BEAM will meet quantitative and qualitative benchmarks of feasibility, acceptability, and program uptake that will motivate implementation of BEAM at greater scale.

We additionally aim to evaluate BEAM’s effectiveness in improving long-term health and psychosocial child and family outcomes relative to two population-based control cohorts. Using a natural experiment, we will construct ‘population-average’ and ‘risk-matched’ control cohorts from administrative data in the province of Manitoba, Canada. The ‘population-average’ cohort will consist of parents who match the basic demographics of BEAM participants and their children (e.g., age, number of children, etc.), while the ‘risk-matched’ cohort will consist of parents who match the basic demographics as well as the physical health, mental health, developmental, and service utilization characteristics of BEAM participants and their children (e.g., vaccination records, mental illness diagnoses, school literacy/numeracy benchmarks, hospitalization records). Administrative data will be drawn from childbirth (as early as January 2018) to as much as five years post-intervention (with an end date of June 2030). We hypothesize that participants who receive BEAM will evidence improvements in administrative measures of physical health, mental health, and developmental outcomes relative to the population-average and risk-matched cohorts.

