### Outcomes {12}

#### Primary outcomes

This trial has co-primary aims evaluating: (1) BEAM’s effectiveness in improving parent mental health outcomes, and (2) the implementation of BEAM in the community through metrics of feasibility, acceptability, and uptake.

The co-primary effectiveness outcome is mean change in a composite score of parent mental health symptoms across all four timepoints: pre-intervention (T1), post-intervention (T2), 6-month follow-up (T3), and 12-month follow-up (T4). This composite score will be defined uniquely for each participant using a weighted average of their pre-intervention (T1) mental health profile (i.e., self-report symptoms of depression, anxiety, anger, and sleep problems). Pre-intervention symptoms above established clinical cut-offs will be mean-centred, standardized, and included in the participant’s composite mental health symptom score weighted by the symptom’s pre-intervention severity. In this way, the primary outcome will track mean change in each participant’s most clinically elevated pre-intervention symptoms. Depressive symptoms will be assessed using the PHQ-9 [42], a 9-item self-report measure of depression severity. Each item taps the frequency of depressive symptoms over the past week on a 4-point Likert scale (0 = *not at all* to 3 = *nearly every day*). Total scores range from 0 to 27, with higher scores indicating greater depressive symptom severity. A PHQ-9 cut-off score of ≥ 10 will identify participants with clinically elevated symptoms of depression. Anxiety symptoms will be assessed using the GAD-7 [43], a 7-item self-report measure of anxiety severity. Each item taps the frequency of anxiety symptoms over the past week on a 4-point Likert scale (0 = *not at all* to 3 = *nearly every day*). Total scores range from 0 to 21, with higher scores indicating greater anxiety symptom severity. A GAD-7 cut-off of ≥ 10 will identify participants with clinically elevated symptoms of anxiety. Anger will be assessed using the PROMIS Short Form, a 5-item self-report measure of anger frequency and severity [45]. Total scores range from 5 to 25, with higher scores indicating more anger. A PROMIS cut-off ≥ 16 will identify participants with clinically elevated anger symptoms. Sleep problems will be measured using the PROMIS Sleep Disturbance Scale, an 8-item self-report measure of sleep disturbances [48]. Total scores range from 8 to 40, with higher scores indicating greater severity of sleep disturbance. A PROMIS Sleep Disturbance Scale cut-off ≥ 30 will identify participants with clinically elevated sleep disturbances. All outcome measures are outlined in Table 1. We have obtained the necessary licenses to use all instruments mentioned in the protocol, ensuring compliance with their respective copyright and usage requirements.

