#### Secondary outcomes

Secondary outcomes include mean change in parent mental health symptoms, harsh parenting behaviour, child mental health symptoms, child development, and child school readiness across all four timepoints: pre-intervention (T1), post-intervention (T2), 6-month follow-up (T3), and 12-month follow-up (T4). Change in parent mental health symptoms of depression, anxiety, anger, and sleep problems will be respectively measured by the PHQ-9, GAD-7, PROMIS Short Form, and PROMIS Sleep Disturbance scales, as previously defined [42, 43, 45, 48]. Mean change in substance use will also be assessed using the 10-item Alcohol Use Disorders Identification Test (AUDIT) [50] and 8-item Cannabis Use Disorders Identification Test – Revised (CUDIT-R) [51]. The AUDIT measures frequency of alcohol consumption, drinking behaviours, and alcohol-related psychological features. Total scores on the AUDIT range from 0 to 40, with higher scores indicating more severe alcohol use problems. The CUDIT-R measures frequency of cannabis consumption, problems, dependence, and cannabis-related psychological features. Total scores on the CUDIT-R range from 0 to 40, with higher scores indicating more severe cannabis use problems.

Other secondary measures include mean change in parenting stress and harsh parenting across all four timepoints: pre-intervention (T1), post-intervention (T2), 6-month follow-up (T3), and 12-month follow-up (T4). Mean change in parenting stress will be assessed using the 36-item PSI-4-SF [44], a self-report measure of parental stress due to individual parent and child factors as well as parent–child interactions. Total PSI-4-SF scores range from 36 to 180, with higher scores indicating higher levels of parenting stress. Mean change in harsh parenting disciplinary practices will be assessed using the Parenting Scale [52], a 30-item self-report measure that assesses parenting behavior and dysfunctional discipline in parents with young children. Total scores range from 30 to 210, with higher scores indicating higher levels of ineffective discipline practices.

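### The primary composite gives no weight at T2 to T4 to a scale below cut-off at T1, so it cannot register newly emerging symptoms, although the hypothesis concerns parent mental health in general

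*Protocol article*

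**What the plan says.** Under Primary outcomes, the protocol article sets the composite separately for each parent: "This composite score will be defined uniquely for each participant using a weighted average of their pre-intervention (T1) mental health profile". Entry depends on T1 status: "Pre-intervention symptoms above established clinical cut-offs will be mean-centred, standardized, and included in the participant’s composite mental health symptom score", and what enters is "weighted by the symptom’s pre-intervention severity". The cut-offs are stated, for example "A PHQ-9 cut-off score of ≥ 10 will identify participants with clinically elevated symptoms of depression" and "A GAD-7 cut-off of ≥ 10 will identify participants with clinically elevated symptoms of anxiety"; for PROMIS Anger the threshold is 16 and for PROMIS Sleep Disturbance 30. The article then gives the purpose: "In this way, the primary outcome will track mean change in each participant’s most clinically elevated pre-intervention symptoms".

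Objectives {7} words the aim more widely, as "determining BEAM’s effectiveness in improving parent mental health challenges", with a hypothesis of improved self-reported mental health. Statistical methods {20a} likewise tests for a reduction in parent mental health symptoms from T1 to each of T2, T3 and T4. Under Secondary outcomes, each scale is also followed separately: "Change in parent mental health symptoms of depression, anxiety, anger, and sleep problems will be respectively measured".

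**The concern.** The inclusion rule is applied once, at T1. After that a scale is either in a parent's composite for the whole study or out of it. A parent can therefore lose one clinical symptom, acquire another, and count as improved on the outcome that carries the effectiveness conclusion. The composite answers whether the symptoms a parent started with fell. The stated hypothesis asks whether the parent's mental health improved. In a single-arm trial meant to inform nationwide scaling, a favourable answer to the first question could be reported as an answer to the second.

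**Working it through.** The plan gives no figure on this point, so there is none to reproduce. The rule and the cut-offs come from Primary outcomes; every SD, prevalence and correlation below is an assumption.

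**1. One parent.** Take PHQ-9 16 to 8 and GAD-7 6 to 14, with anger and sleep unchanged and below cut-off. Assume a T1 SD of 5 on both moving scales. Only PHQ-9 is elevated at T1, so its weight is 1.
- Planned composite: (8 − 16)/5 = −1.6 SD.
- Equal-weight mean of four scales: (−1.6 + 1.6 + 0 + 0)/4 = 0.0 SD.

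The sign of the planned composite is certain here because one scale carries all the weight. With two included scales the change is w·Δ1 + (1 − w)·Δ2, and the sign depends on both. In a no-change simulation (between-scale correlation 0.3 to 0.7, retest correlation 0.5 to 0.85), 87 to 91% of parents who lost one elevated scale and gained another were scored as improved.

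**2. How much lies outside the composite.** Simulation of four normal scales with no mean change: 40 to 60% above each cut-off at T1, between-scale correlation 0.4 to 0.6, T1–T2 stability s of 0.6 to 0.8. Among parents with a composite:
- at least one scale outside it: 61 to 86%;
- a newly clinical scale at follow-up that it cannot see: 25 to 38%.

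**3. Which way the errors run.** Two models of change, both with zero mean change and the same SD of change, √(2(1 − s)), which is 0.89 for s = 0.6 and 0.63 for s = 0.8.

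| | Stationary scores (regression to the mean present) | Change independent of T1 level (absent) |
|---|---|---|
| Composite improved, four-scale mean unchanged or worse | 8 to 16% | 4 to 8% |
| The reverse | 1 to 4% | 4 to 8% |
| Mean change in composite | −0.12 to −0.38 SD | about 0.00 SD |

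A closed form for a single scale agrees with the first column. With standardized scores, the expected change given z1 is −(1 − s)·z1, and the mean of z1 above cut-off c is φ(c)/(1 − Φ(c)).
- 50% above cut-off: mean 0.798, so the fall is 0.4 × 0.798 = 0.32 SD for s = 0.6 and 0.2 × 0.798 = 0.16 SD for s = 0.8.
- 40% above: mean 0.966, falls 0.39 and 0.19 SD.
- 60% above: mean 0.644, falls 0.26 and 0.13 SD.

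**4. The alternative under the same conditions.** Over all simulated parents the four-scale mean changes by about zero. Restricted to parents with at least one elevated scale, it still falls slightly (0.02 to 0.15 SD under the wider assumptions of step 1), because that restriction is itself a selection on T1.

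**The case against.** The strongest reply is that the design is deliberate and openly stated. Tracking each parent's own presenting symptoms is a recognizable target for a transdiagnostic programme that enrols on any of several elevations, and the article does not contradict itself. This stands: the difficulty is the fit between the outcome and the wider hypothesis, not an inconsistency in the rule.

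Three stronger readings are tempting, and the documents do not support them.
- *Deterioration is hidden from the trial.* It is not. Secondary outcomes lists all four scales, and Statistical methods {20a} applies the same mixed model to each, with no restriction to parents above cut-off. A mean rise on any scale would be estimated. What remains is that these results do not enter the primary outcome, and that separate means do not show how many parents exchanged one clinical symptom for another.
- *The outcome favours BEAM even apart from regression to the mean.* The blind spot exists with perfectly measured scores, but the net tilt does not. When change is independent of T1 level, errors in the two directions are equal and the mean composite change is zero. The share with a newly clinical scale is then still 22 to 34%, so that share measures what the composite misses, not bias.
- *Any parent who swaps symptoms is scored as improved.* This is certain only when the resolved scale was the sole elevated one.

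**Conclusion.** The point holds as a mismatch between outcome and hypothesis. By its stated rule, the primary composite cannot register a symptom that emerges after T1, whatever the assumptions. The sizes are illustrative: 61 to 86% of parents with a scale outside the composite, 25 to 38% with an unseen newly clinical scale, and a fall of 0.12 to 0.38 SD with no true change. They rest on assumed prevalence, correlation and stability, since the article gives none of these. The fall is regression to the mean induced by selecting scales at T1, and with no control arm in the primary comparison it cannot be separated from benefit. A fixed all-scale composite over all parents does not carry that T1 selection. It would not remove any regression that follows from enrolling parents for high scores at T0.

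**What to change.** Prespecify, beside the individualized composite:

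1. A fixed equal-weight composite of all four scales, standardized on the T1 mean and SD and analysed with the same mixed model. Compute it for every parent, including those with no scale above cut-off at T1; limiting it to parents who have an individualized composite would bring back part of the selection.
2. The proportion of parents with any newly clinical scale at T2, T3 and T4.
3. Wording that reports the individualized result as change in the symptoms elevated at T1, and reads any general statement about parent mental health in light of the all-scale result.

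A second compulsory success criterion is not proposed; it would alter the primary decision rule after enrolment began, without a power check.

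Cost: a little more analysis and no new data, because Table 1 schedules all four scales at T1 to T4. The all-scale effect will probably look smaller, since it includes scales with little room to fall.

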***Back-end data tracking***	
Video Engagement	Total time spent watching videos
Forum Engagement	• Number of posts made on forum • Number of comments made on forum
Other	Exploratory measures pending feasibility in the app
***Coach/Research Team tracking***	
Weekly Survey Completion	Number of weekly surveys completed
Coach Engagement	• Number of 1:1 sessions attended • Number of times contacting coach and the type of contact
Drop-in Session Engagement	Number of drop-in sessions attended
Systems Navigator Engagement	Number of times systems navigator was engaged, and the types of support provided
***Self-Report Measures***	
App Usability	Self-report: mHealth App Usability Questionnaire
Engagement	Survey questions developed for BEAM
Satisfaction	Survey questions developed for BEAM
Therapeutic Alliance	Brief Revised Working Alliance Inventory
***Focus groups***	
Program Feasibility, Acceptability, Barriers, Facilitators	Open-ended questions developed for BEAM

#### Secondary outcomes

Secondary outcomes include mean change in parent mental health symptoms, harsh parenting behaviour, child mental health symptoms, child development, and child school readiness across all four timepoints: pre-intervention (T1), post-intervention (T2), 6-month follow-up (T3), and 12-month follow-up (T4). Change in parent mental health symptoms of depression, anxiety, anger, and sleep problems will be respectively measured by the PHQ-9, GAD-7, PROMIS Short Form, and PROMIS Sleep Disturbance scales, as previously defined [42, 43, 45, 48]. Mean change in substance use will also be assessed using the 10-item Alcohol Use Disorders Identification Test (AUDIT) [50] and 8-item Cannabis Use Disorders Identification Test – Revised (CUDIT-R) [51]. The AUDIT measures frequency of alcohol consumption, drinking behaviours, and alcohol-related psychological features. Total scores on the AUDIT range from 0 to 40, with higher scores indicating more severe alcohol use problems. The CUDIT-R measures frequency of cannabis consumption, problems, dependence, and cannabis-related psychological features. Total scores on the CUDIT-R range from 0 to 40, with higher scores indicating more severe cannabis use problems.

Other secondary measures include mean change in parenting stress and harsh parenting across all four timepoints: pre-intervention (T1), post-intervention (T2), 6-month follow-up (T3), and 12-month follow-up (T4). Mean change in parenting stress will be assessed using the 36-item PSI-4-SF [44], a self-report measure of parental stress due to individual parent and child factors as well as parent–child interactions. Total PSI-4-SF scores range from 36 to 180, with higher scores indicating higher levels of parenting stress. Mean change in harsh parenting disciplinary practices will be assessed using the Parenting Scale [52], a 30-item self-report measure that assesses parenting behavior and dysfunctional discipline in parents with young children. Total scores range from 30 to 210, with higher scores indicating higher levels of ineffective discipline practices.

Mean change in child mental health, development, and school readiness will similarly be measured across all four timepoints. Child mental health symptoms will be assessed at each timepoint using the CBCL [53], a parent-report questionnaire that is used to detect behavioural and emotional problems in children. The CBCL demonstrates adequate internal reliability (α’s ≥ 0.78) and has precedent as a measure of change in intervention research [46, 54–56]. The CBCL includes 99 items in which parents are asked to rate their child on how true each item is from 0 (*not true*) to 2 (*very true or often true of the child*). Possible scores range from 0 to 198, where higher scores indicate more mental health symptoms. Items are scored on the following syndrome scales: emotionally reactive, anxious/depressed, somatic complaints, withdrawn, attention problems, aggressive behaviour, and sleep problems. The CBCL total score and syndrome scores will be examined. Change in child socioemotional development will be assessed using the Ages and Stages Questionnaires: Socioemotional, Second Edition (ASQ:SE-2), a screening tool that identifies socioemotional challenges across a range of developmental domains [57]. Different versions of the ASQ:SE-2 exist depending on the age of the child. For this trial, five versions of the ASQ:SE-2 cover the age of all eligible children. Depending on version, the ASQ:SE-2 has approximately 30 items which sum to a total score. Higher scores represent more severe socioemotional challenges. Change in child school readiness will be measured by the Ages and Stages Questionnaire, Third Edition (ASQ-3), a parent-report screening tool that taps child developmental progress across domains of communication, motor, problem solving, and personal-social [57]. Nine versions of the ASQ-3 cover the age of all eligible children. The ASQ-3 contains 30-items which sum to a total score. Higher scores represent a greater number of met developmental milestones, indicative of school readiness.

#### Exploratory outcomes

Exploratory outcomes include changes in positive parenting behaviour and social support [58]. Change in positive parenting will be measured by four items of the PSI-4-SF that tap parenting self-efficacy [44, 59, 60]. Change in social support will be measured using the SSEQ [61]. Total scores range from 0 to 80, with higher scores representing greater social support effectiveness [57].

Exploratory mediators and moderators of change include discrimination, adverse childhood experiences, concomitant service utilization, food insecurity, housing instability, therapeutic alliance, and participant sociodemographic and socioeconomic characteristics (Table 3). Discrimination will be measured using the Everyday Discrimination Scale (EDS), a 5-item self-report scale measuring subjective experiences of discrimination [62]. Adverse childhood experiences will be assessed with the Adverse Childhood Experiences (ACEs) questionnaire. [63]. Total scores range from 0 to 10, with higher scores indicating more adverse experiences in early childhood. Concomitant service utilization will be measured by a self-report questionnaire developed for the BEAM program that is meant to supplement the collected administrative data. The service utilization questionnaire asks about the total number of contacts and total contact hours with a variety of acute (e.g., hospitalization), primary (e.g., family doctor visit), and community-based services (e.g., child care centres, family resource centres). Food insecurity will be assessed by the Household Food Security Survey Module (HFSSM) from the Canadian Community Health Survey [64]. The HFSSM taps household food insecurity over the past 12 months. Total scores range from 0 to 16, with higher scores indicating greater food insecurity. Such use of questionnaires from the Canadian federal government will enable comparison of BEAM participant food security and housing stability with Canadian population averages. Housing instability will be measured by the Housing Instability Scale (HIS) [65]. The HIS taps housing instability over the past 6 months. Total scores range from 0 to 7, with higher scores indicating greater housing instability [66]. Therapeutic alliance between the peer coaches and participants will also be assessed using the Brief Revised Working Alliance Inventory (BR-WAI), a 16-item measure assessing bonds, tasks, and goals within the therapeutic relationship [67]. Finally, participant sociodemographic and socioeconomic information will be assessed by a questionnaire developed for the BEAM program. This questionnaire asks about parent, child, and family demographics, household income, parent marital status, educational attainment, employment status, and childcare.

**Table 3 Tab3:** Sociodemographic and Socioeconomic Variables

Construct	Metric	T0	T1	T2	T3	T4
***Self-Report Measures***						
Sociodemographic information (constructs include age, income, marital status, education, …)	Sociodemographic Questionnaire (developed for BEAM)		X	X	X	X
Service Utilization (constructs include contact hours with acute, primary, community-based care services)	Service Utilization Questionnaire (developed for BEAM)		X	X	X	X
Food Security	Household Food Security Survey Module (HFSSM; 2024 Canadian Community Health Survey)		X	X	X	X
Housing Stability	Housing Instability Scale (HIS)		X	X	X	X
Discrimination	Everyday Discrimination Scale (EDS)		X	X	X	X
Childhood Experiences	Adverse Childhood Experiences		X			

### Administrative measures

This trial of BEAM will also examine changes in family health and education, as measured using de-identified administrative-linked data from provincial government health and social service records in partnership with the Manitoba Centre for Health Policy (MCHP). This means that participant self-report data collected as part of the BEAM program will be linked to their provincial government health and social services records from the Manitoba Population Research Data Repository. Firstly, this linkage enables the longitudinal analysis of a broader scope of participant family physical health, mental health, and education outcomes from childbirth to up to five years post-intervention (June 2030). Secondly, this linkage enables the longitudinal comparison of BEAM participants to two population-based cohorts (‘population-average,’ ‘risk-matched’ control cohorts) of families who did not participate in BEAM, allowing examination of how BEAM may lead to lasting family improvements in psychological, social, and physical health. Participants are not required to consent to administrative data linkage to participate in BEAM. Those who do not consent will be excluded from the BEAM population-based cohort, but there is no way to ensure that they will be excluded from a control cohort. This is because those who opt out may not provide sufficient demographic information (e.g., Personal Health Identification Number [PHIN], age, postal code) to ensure control cohort exclusion. Preliminary data shows more than 80% of participants opting in. Further, every possible step will be taken to remove any BEAM participants from the control cohorts (e.g., by cross-referencing participant full names). Our analysis will be securely conducted by trained analysts from the Manitoba Centre for Health Policy (MCHP), the custodians of the Manitoba Population Research Data Repository.

Administrative data will include measures of family health and wellbeing (i.e., socioeconomic status, perinatal health, mental health, and substance use) assessed through the Families First Home Screening Form. Parent medical care including, hospitalizations, emergency visits, prescription medications, physical illness (e.g., atopic dermatitis), mental illness (i.e., mood, anxiety, substance use, psychotic disorders), and cause of death will be assessed using Hospital Abstracts Data, Medical Services Data, the Mental Health Management Information System (MHMIS), the Drug Program Information Network (DPIN), and Vital Statistics Mortality Registry Data. Child medical care including traumatic injury, hospitalizations, emergency visits, physical illness (e.g., lower respiratory tract infection), mental and neurodevelopmental disorders (e.g., mood, anxiety, trauma-related disorders, ADHD), prescription medications, and vaccinations will be assessed using the Mental Health Management Information System (MHMIS), Medical Services Data, and Hospital Abstracts Data, and the Manitoba Immunization Registry. Measures related to child development including age-appropriate grade, literacy, numeracy, special needs funding status, academic accommodations, health and psychosocial development, child care centre use, family income assistance, and family employment will be measured through enrolment, Marks and Assessment (STS/ICAB), Early Developmental Instrument (EDI), Child Day Care Program, and Manitoba Education Special Needs. Finally, Child Family Services (CFS) and parent justice involvement including days in CFS care, charges, and charge categories may be examined using the Child and Family Services Information System (CFSIS) and Justice Prosecution Information and Scheduling Management (PRISM), pending indication of interest and approval from the First Nations Health and Social Secretariat of Manitoba’s Health Information Research Governance Committee. Administrative data will also include basic demographic information such as date of birth, biological sex, postal code of residence, and family registration number. These data will be drawn from the Manitoba Health Insurance Registry [49, 67].

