Analysis of administrative-linked outcomes will enable comparisons between BEAM families and those families in ‘population-average’ and ‘risk-matched’ control cohorts drawn from MCHP’s provincial administrative database. While the ‘population-average’ control cohort will be comprised of parents who match the basic demographics of BEAM participants and their children (e.g., age, number of children), the ‘risk-matched’ control cohort will consist of parents of young children who match the demographics, physical health, mental health, child developmental, and service utilization characteristics of BEAM participants and their children. This will be accomplished in consultation with MCHP by matching Manitoban families in the administrative database to BEAM families on these risk factors. These matching criteria will be developed using MCHP’s high-dimensional propensity scores matching algorithm (hdPSs) which, across multiple algorithmic iterations, identifies risk factors that are correlated with the features of the participants who have enrolled in the BEAM program [71]. This data-driven propensity score development strategy is commonly used and will allow our team to match BEAM participant risk to non-BEAM participants in the community. Comparing trajectories in health and social outcomes between BEAM participants, ‘risk-matched’ controls, and ‘population-average’ controls will generate knowledge about the extent to which children experience stable, cumulative, or “sleeper” (i.e., not observable until after developmental time periods) benefits over time. If we find children experience diminishing effects such that program benefits are only present in the first year, this may indicate that further intervention is required to sustain program achievements. All administrative-linked analyses will be conducted by MCHP statisticians.

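### The administrative comparison analyses only BEAM parents who consent to record linkage but states its hypothesis for all who receive BEAM; opt-in may shift the result in an unknown direction, and some treated opt-outs may remain among the controls

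*Protocol article*

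**What the plan says.** The Objectives section states this hypothesis: "participants who receive BEAM will evidence improvements in administrative measures of physical health, mental health, and developmental outcomes relative to the population-average". A second comparator, the risk-matched cohort, is named in the same sentence. The population named there is everyone who receives the programme.

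The Administrative measures section makes linkage a separate choice: "Participants are not required to consent to administrative data linkage to participate in BEAM". On decliners it says: "Those who do not consent will be excluded from the BEAM population-based cohort, but there is no way to ensure". What cannot be ensured, the sentence goes on, is their absence from a control cohort. The reason given is: "This is because those who opt out may not provide sufficient demographic information". The section reports the uptake so far, "Preliminary data shows more than 80% of participants opting in", and promises mitigation: "every possible step will be taken to remove any BEAM participants from the control cohorts (e.g., by cross-referencing participant full names"). It also describes the control cohorts as consisting "of families who did not participate in BEAM, allowing examination of how BEAM may lead to lasting family improvements".

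Under Statistical methods {20a}: "Analysis of administrative-linked outcomes will enable comparisons between BEAM families and those families in" the two control cohorts, which come from the provincial administrative database. The population-average cohort is matched on basic demographics. The risk-matched cohort is built with a high-dimensional propensity score on recorded characteristics. The intention-to-treat and maximum-likelihood provisions concern missing data among participants; they do not mention linkage consent.

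**The concern.** The self-report analysis is single-arm, so this comparison is where a contrast with families outside BEAM would come from. It is meant to support statements about stable, cumulative or delayed benefit, with records running to June 2030.

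The stated rule has two consequences. The analysed BEAM cohort is a self-selected part of the population in the hypothesis. Consent may depend on things that the records do not hold, such as current symptom scores, childhood adversity or food insecurity, and matching on records cannot balance those. In addition, a treated family that declines linkage moves from the BEAM side to the pool from which controls are drawn. Where such families are matched in, the contrast shrinks towards no difference.

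**Working it through.** **Inputs from the protocol.** Target enrolment is 400 (Sample Size). Opt-in is above 80% in preliminary data (Administrative measures); I use p = 0.80 as the floor. No control ratio, no difference between opt-ins and opt-outs, and no sample size or power for the administrative comparison are given. There is therefore no planned figure to reproduce, and the ranges below are assumptions.

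**Numbers linked.** 400 × 0.80 = 320 linked; at most 400 − 320 = 80 opt-outs.

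**Opt-in shift.** Let s be the opt-in minus opt-out difference in SD on factors outside the records. The mean of all enrollees is p × (opt-in mean) + (1 − p) × (opt-out mean), so

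linked mean − all-enrollee mean = (1 − p) × s.

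| Assumed s | p = 0.80 | p = 0.90 |
|---|---|---|
| 0.2 SD | 0.04 SD | 0.02 SD |
| 0.3 SD | 0.06 SD | 0.03 SD |
| 0.5 SD | 0.10 SD | 0.05 SD |

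This is the distance between those analysed and those named in the hypothesis. It becomes bias against controls only if the controls match all enrollees, rather than the consenters, on the same unrecorded factors. The sign of s is not known.

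**Contamination.** Let r be the number of controls per linked family and q the share of opt-outs that are matched in and not removed. Then

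c = 80q / (320r), and estimated effect / true effect = 1 − c,

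assuming that opt-outs benefit as much as linked families and otherwise resemble the other controls.

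| q | r = 1 | r = 5 |
|---|---|---|
| 1.00 (every opt-out, none removed) | c = 25%, ratio 0.75 | c = 5%, ratio 0.95 |
| 0.25 | c = 6.25%, ratio 0.94 | c = 1.25%, ratio 0.99 |
| 0.05 | c = 1.25%, ratio 0.99 | c = 0.25%, ratio 1.00 |

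**Data available for a check.** Under Screening and enrolment, a parent counts as enrolled only after completing the pre-test assessment. T1 self-report (Tables 1 and 3) should therefore exist for opt-ins and opt-outs alike.

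**The case against.** The case on the other side is substantial.

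- The protocol itself discloses the contamination, explains its cause, reports high opt-in and commits to removing participants by name. What is left pushes towards no difference. This stands: the 25% figure needs 1:1 matching, every opt-out matched in and none removed, so a reader should not infer that a quarter of the effect is likely to be lost.
- A reader might infer that opt-in selection will pass for a BEAM benefit and put a false-positive rate on it. For example, a 0.10 SD shift with 320 against 320 gives SE = √(2/320) = 0.079 and about 24% rejections at two-sided 0.05. The documents do not support that step. The planned contrast is with matched non-participants, not with all enrollees; selection could favour or disfavour BEAM; and records reach back to childbirth, as early as January 2018, so comparing trajectories may remove stable differences.
- That control families face no consent step is inferred from their being drawn from the provincial database. The protocol does not say so.
- Child-welfare and justice records are both conditional on interest and approval, so they cannot be assumed to be among the data that deter consent.
- Weights, matching ratios and bias bounds are often left to an analysis plan that is not shown. Their absence is not the point. What remains is a stated rule that drops decliners from the BEAM cohort, beside a hypothesis worded for all recipients and a control definition that the same section admits it cannot guarantee.

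**Conclusion.** The point holds in a limited form. The administrative result will describe linkage consenters, not all who receive BEAM, and may be shifted relative to controls by an amount and in a direction that the documents do not determine. At 80% opt-in, the distance from all enrollees is 0.04 to 0.10 SD for an assumed gap of 0.2 to 0.5 SD. Reading that as bias needs the further assumption that controls resemble all enrollees on unrecorded factors, and baseline records may take out part of it. Dilution by treated controls is at most 25% at 1:1 and 5% at 1:5, and probably far less. The two can act in opposite directions, but there is no ground for assuming that they cancel. The Abstract places long-term administrative outcomes under a secondary aim; the co-primary outcomes are not touched. This is a cheap improvement, not a flaw that invalidates the comparison.

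**What to change.** In the paragraph on administrative-linked outcomes under Statistical methods {20a}:

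1. Compare opt-ins with opt-outs on the T1 self-report data held on all enrolled parents (symptom scores, sociodemographics, service use, food and housing insecurity, childhood adversity). Opt-outs may have withheld items such as age or postal code, so report completeness as well.
2. Add a sensitivity analysis with inverse-probability-of-opt-in weights estimated from those T1 data. Apply each linked family's weight to its matched controls too, so that the matched sets stay balanced. The research team fits the model and sends the Manitoba Centre for Health Policy weights for linked families only; no opt-out's data need leave the team for this. The weights correct only for predictors measured at T1.
3. Report a worst-case contamination bound, effect / (1 − c), with c = opt-outs not confirmed removed / number of controls. Label it as an upper limit, because it treats every such parent as a control.
4. State the main administrative conclusion as applying to participants who consented to linkage.

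The cost is a few lines of text, one table and one weight variable. The downsides are slightly wider intervals in the weighted analysis and a narrower stated conclusion. The unweighted comparison can remain the main one, and the matching ratio need not be fixed on this account.
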